**Background**

**Anxiety - a public health problem**

Anxiety can be described as an unpleasant feeling of fear, anxiety, tension or pressure. There is hardly anyone who has not experienced anxiety. Many people are troubled, however, of such reactions so often and so intensely that great suffering and limitations in life occurs, which is called anxiety disorders. In the U.S., population studies have shown that within one year 27 million people fulfil the criteria for at least one psychiatric disorder (1). Anxiety disorders are the most common psychiatric diagnosis in women and the second most common in men (2). In addition to suffering for individuals entails anxiety problems a considerable financial burden on society. The annual cost to society of these, such as in terms of sick leave and loss of earnings, is estimated at over 68 billion dollars in U.S. (1).

**Social phobia**

Epidemiological studies have shown that social phobia is the most common psychiatri syndrome in the Western world, with a lifetime prevalence of up to 10-15% (2-4). A person with social phobia is plagued by a fear of being audited or reviewed by others and ending up in the center of attention. Strong anxiety reactions can occur when the individual must perform something when other people, in particular strangers, watch, but also in normal social situations. Speaking before a group, attend meetings, go to a party or seek contact with other typical problem situations. Clinical studies have shown that persons with social phobia have a significantly impaired quality of life as well as problems with social relationships, partner relationships, well-being in the family, and functioning at work (5). Untreated social phobia often follows a chronic course (6) and often precedes other serious psychiatric disorders such as depression and alcohol problems. Social phobia is a widespread disease and also a gender specific problem as the symptoms are more common among women (4). Nausea is also common among the younger population, which may be related to the requirement to perform in social settings has increased in modern society (7). Social phobia has even been called a democracy problem because many victims do not dare to comment or participate in groups.

**Treatment of social phobia**

There are both psychological and pharmacological treatments that are proven effective in social phobia (8). Cognitive-behavioral therapy (CBT) is a structured psychological therapy that has been found to be effective in several controlled studies (8, 9). In CBT the therapist helps to change negative thoughts and beliefs that patients associate with different problem situations while the patient is exposed gradually to situations that arouse anxiety. We have in the past five years developed an Internet-delivered CBT program that has been tested in randomized trials (10-12). These studies show improvements that are fully comparable with those seen in regular face-to-face CBT (9). In the Internet- delivered CBT program the patient works with a self-help manual (13) made available through the Internet, while e-mail correspondence is weekly with a therapist (in a secure system). Patients also have access to an online discussion forum and the program can also be combined with exposure exercises carried out during the group meetings (10). In addition to studies on social phobia (the so-called SOFIE projects), the research also showed similar positive treatment outcomes of Internet-based treatments of panic disorder, tinnitus, chronic pain, depression, bulimia / binge eating disorder, and compulsive gambling.

**Genetic markers and treatment**

A heritability rate of over 30% has been reported in twin studies of social phobia (14). This suggests that genes have an important role in the onset of problems, even though we have no detailed knowledge of how genes, or gene interaction with brain function and environment, contribute to social anxiety. Serotonin transporter gene is a potentially important gene for social phobia. The anxiolytic effects of selective serotonin reuptake inhibitors (SSRIs) appear to be mediated by an inhibition of the serotonin transporter, ie. the protein that återtransporterar serotonin into the presynaptic neuron (15). Transportation of serotonin is largely influenced by genetic factors and there are related differences in the resumption of short and long alleles in the serotonin transporter gene promotor region. People who are homozygous for the long allele (l / l) has an increased reuptake of serotonin compared to those who are carriers of one or two short (s / l or s / s) alleles (16). Several studies have shown that the short allele is associated with higher general anxiety and neural activity in the amygdala (17), ie. a brain region that is strongly associated with emotional reactions such as fear and anxiety (18,19).

We have previously reported that people with social phobia who carry the short allele have a more symptoms of social anxiety, and an increased reactivity in the right amygdala during social anxiety provocation (20). A recent treatment study showed that variation in the serotonin transporter gene was important for how well patients with social phobia responded to treatment with serotonergic drugs (21). We also have new data suggesting that tryptofanhydroxylas-2 (TPH2) gene, coding for serotonin synthesis in the brain, is related to the placebo response in social phobia (22), as well as the amygdala activity (22.23). The TPH2 polymorphism we studied is called the G-703T where the T allele (risk allele) compared to G allele (22.23)

**Purpose**

Currently, it is not known if genetic variation is important in psychotherapeutic treatments such as CBT. This project aims to, in addition to a controlled evaluation of Internet-based CBT, identify if particular serotonin-related genes affect how people with social phobia respond to Internet-based CBT.Since there are few studies that have examined what predicts treatment outcome in social anxiety disorder, it is theoretically and clinically important to study this as well. In the trial we will also develop and include a test of knowledge about social phobia and test the role of therapist experience. This is not described further here as it is not a main ethical consideration.

**Issues**

The project's primary issues are:

1. Is the effect of Internet-based CBT influenced by variation in the serotonin transporter and the TPH2 genes? More specifically,

a) How is the short and long alleles in the promoter region of the serotonin transporter gene related to CBTresponse?

b) How is this related the T and G alleles of the G-703T polymorphism related to CBT response?

2. How the above mentioned genetic variations related to symptom profile at social phobia (before treatment), More specifically,

a) the subset of social phobia (generalized or non-generalized social phobia)

b) severity as measured by social phobia scales

c) the degree of general anxiety as measured by questionnaire

d) the degree of depression measured by questionnaire

e) influence quality of life as measured by questionnaire

Gene analyzes focusing initially on the variation in the serotonin transporter-and TPH2 genes, but also other genes will be evaluated in the exploratory analysis. These will be limited to genes that directly or indirectly affect neurons with the importance of cognitive or emotional reactions (eg those that use dopamine, glutamate, GABA, vasopressin, acetylcholine or norepinephrine as a neurotransmitter).

The project will also to evaluate whether the Internet-based CBT program is effective when compared against an active control group (randomized). In addition to the project study additional predictors of treatment outcome. Previous research has, among other things identified the severity of social anxiety before treatment influenced the outcome. The project will also evaluate the two hitherto unstudied factors that may influence treatment outcome, namely the acquired knowledge (psychoeducation) and therapeutic alliance. The latter predictors will be measured by questionnaire.

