**Screening, pretreatment assessment and randomization**

The screening process will follow the procedures from our recent study in the SOFIE project (No. 2005:187). When the subject has expressed an interest, a code is sent out which gives access to the portion of the site on which the screening instruments available. The participant answers the first forms: Social Phobia Screening Questionnaire-SPSQ (3) and Montgomery Asberg Depression Rating Scale-MADRS (24). Participants must meet the criteria for social phobia using the international classification system Diagnostic and Statistical Manual of Mental Disorders, 4th edition (DSM-IV) (25). This is mainly determined by SPSQ form that has been shown to have good sensitivity and specificity in comparison with the structured diagnostic interviews. In addition, we include a telephone screening, which follows a structured clinical interview, Structural Clinical Interview for DSM-IV - Axis I Disorders: SCID I (26). Individuals with current major depression and / or suicide-prone persons will be excluded from the study. Furthermore, the subject will be asked to submit a signed consent form to the research group. The constent form involves consent to do genetic analyzes and stores saliva samples in a biobank, the processing of personal data concerning him / her in accordance with the Data Protection Act and that he / she hs received information on the website about how the study.

The subjects meeting the inclusion criteria will then be randomized into two groups so that half may begin directly with the Internet-based self-help treatment program (treatment cycle 1) while the other half gets allocated to the control group which involves participation in a moderated discussion forum on the Internet for nine weeks after which they are treated as usual with the Internet-based program (treatment session 2). The latter group controls in this manner for the time and measurement.

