**Evaluation**

Posttreatment measurements are made in connection with the final module completed. Follow up with a short phone interview and form occurs after 12 and 24 months. The latter is done to evaluate the longer-term treatment effects and to compare these with the short-term effects. Pre-, post-and follow-up measurements will be made with established international form (see above). An attempt will be made to try to identify predictors of treatment success and factors that may predict which individuals this type of treatment is best suited for.

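### Primary issue 1 asks whether genes influence the effect of CBT, but 1a and 1b specify it as allele versus CBT response, with no contrast to the randomised control

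*Protocol*

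**What the plan says.** The parent question of primary issue 1 (Protocol, Issues) is "Is the effect of Internet-based CBT influenced by variation in the serotonin transporter and the TPH2 genes". The protocol then makes it more specific in two parts. Part 1a asks "How is the short and long alleles in the promoter region of the serotonin transporter gene related to CBTresponse", and part 1b asks about "the T and G alleles of the G-703T polymorphism related to CBT response". The term CBT response is not defined.

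The randomised control is given other work. In the same section it serves to "evaluate whether the Internet-based CBT program is effective when compared against an active control group (randomized", a separate question listed after the primary issues. Under Screening, pretreatment assessment and randomization its role is described in one sentence: "The latter group controls in this manner for the time and measurement". The Subjects section says the sample gives a fair chance of detecting effects of gene variants and gene-gene interactions on treatment response. It does not mention a gene-by-arm comparison, and no other section does.

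Under Genetic markers and treatment, the protocol cites new data suggesting that the TPH2 gene "is related to the placebo response in social phobia".

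**The concern.** In a randomised trial the effect of a treatment is the difference from control. A gene influences that effect if the difference varies by genotype, which is a genotype-by-arm interaction. How alleles relate to improvement among people given CBT is a different quantity. It adds together any genotype-related difference in improvement that would have occurred anyway (natural course, regression to the mean, repeated measurement, placebo response) and any difference specific to CBT.

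The protocol gives a reason to expect the first component for each gene. For TPH2 it is the suggested placebo link. For the serotonin transporter, the background says short-allele carriers have more social anxiety symptoms, and the Issues section says severity before treatment influenced outcome. An allele could therefore track change through baseline severity alone.

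At stake is the headline genetic conclusion. A gene that predicts improvement under any condition could be reported as moderating CBT, although the trial has a nine-week concurrent control that could help tell the two apart. The Significance section expects treatment implications from this question.

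**Working it through.** **1. The plan's own figure.** The only sample-size figure is 125 per arm, said to rest on a power calculation whose inputs are not given, so it cannot be reproduced. Back-solving for a plain two-arm comparison (two-sided 5%, 80% power, SD 1): (1.960 + 0.842) × √(2/125) = 0.354 SD. The point does not depend on this figure.

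**2. What each test estimates.** Let *a* be the genotype difference in improvement that is not specific to CBT, and *s* the part specific to CBT.
- Among CBT-treated people the genotype difference is *a* + *s*.
- Among controls it is *k*·*a*, where *k* is the share of the non-specific part that the forum condition also produces.
- The genotype-by-arm contrast is *s* + (1 − *k*)·*a*. It equals *s* only if *k* = 1.

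**3. Inputs.** From the protocol: 125 per arm; controls receive CBT after nine weeks, so up to 250 are treated over both rounds. Assumed, because the protocol gives no figures: 36/64 genotype split, every participant genotyped, no dropout, two-sided 5%, *a* = 0.3 SD of change, *s* = 0.

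**4. Standard errors (SD units).** 1/0.36 + 1/0.64 = 4.340.
- Treated only, n = 125: √(4.340/125) = 0.186
- Treated only, n = 250: √(4.340/250) = 0.132
- Interaction, 125 per arm: √(2 × 4.340/125) = 0.264

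**5. Probability of a significant result when the gene does not modify the CBT effect.** Formula: Φ(δ/SE − 1.96) + Φ(−δ/SE − 1.96).

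| Test | δ | δ/SE | Probability |
|---|---|---|---|
| Treated only, n = 125 | 0.3 | 1.61 | 0.36 |
| Treated only, n = 250 | 0.3 | 2.28 | 0.62 |
| Treated only, n = 250 | 0.2 | 1.52 | 0.33 |
| Treated only, n = 250 | 0.4 | 3.04 | 0.86 |
| Interaction, *k* = 1 | 0 | 0 | 0.05 |

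With the smaller genotype group at 20% to 50% and saliva uptake of 80% to 100%, the treated-only probabilities at 0.3 SD run from 0.22 to 0.39 (CBT arm) and from 0.40 to 0.66 (both rounds).

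**6. When the forum produces less of the non-specific part.** With *a* = 0.3 SD:
- *k* = 0.5 leaves 0.15 SD in the interaction: 0.15/0.264 = 0.57, rejection about 0.09.
- *k* = 0 leaves 0.3 SD: 0.3/0.264 = 1.14, rejection about 0.21.

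So the 5% holds only when the shift is equal in both arms.

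**7. Price in precision.** The difference detectable with 80% power is 2.80 × SE: 0.52 SD (treated, n = 125), 0.37 SD (treated, n = 250) and 0.74 SD (interaction). Over the same range of genotype shares and uptake, power for a true interaction of 0.5 SD is 0.29 to 0.51.

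**The case against.** CBT response is undefined. 1a and 1b name no population, model or change score and do not exclude controls. They sit under a parent question about the effect of CBT and might only be naming the two polymorphisms. The text is a rough translation, so the gap between effect and response is weak evidence of a fixed analysis decision. A statistical analysis plan, not available here, could define response relative to control or specify the interaction. Prediction is also a stated aim (Purpose, Significance), and an association among treated people answers it properly.

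Most of this stands as a limit on the point. It does not remove it: the protocol itself goes from effect to response and nowhere ties the control to the gene question, so a later plan that follows 1a and 1b literally would answer a different question from the one asked.

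Four stronger readings are tempting, and the document does not support them:
- *That the protocol expressly restricts the gene analysis to treated people.* It does not; that is the natural reading of an undefined term.
- *That TPH2 is an established placebo marker.* The protocol says only that new data suggest a link.
- *That the control arm fully separates CBT from placebo.* The control is a moderated forum, while CBT participants also have e-mail therapists, so expectancy and contact may differ between arms.
- *That the same error is shown in the search for "factors that may predict which individuals this type of treatment is best suited for" (Evaluation).* That sentence describes an attempt and fixes no method.

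**Conclusion.** The point holds as a mismatch between a primary question and its stated specification. The design itself is not at fault: volunteers in both arms are genotyped before treatment, so the needed contrast is available for the first nine weeks. On the natural reading of 1a and 1b, a positive finding would show that genotype predicts outcome after CBT, not that it modifies the CBT effect.

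The rejection probabilities of about 36% and 62%, against 5%, illustrate the possible size. They rest on an assumed split, full genotyping and an assumed 0.3 SD shift equal in both arms, none of which is in the protocol. That a treated-only association mixes the two components does not depend on those values. Whether the low-powered interaction should become the sole primary gene test is a trade-off for the sponsor, and the document does not settle it.

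**What to change.** Add to issue 1 a genotype-by-arm test on LSAS at week 9, in the genotyped participants of both arms, adjusted for baseline LSAS. Rest any statement that a gene influences the effect of CBT on that test alone. Keep the association of genotype with change in all CBT-treated participants (rounds 1 and 2), labelled as prediction of outcome after CBT. The same labelling would suit the predictor work under Evaluation.

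State three limits alongside it:
- The interaction is imprecise: about 0.74 SD detectable with 80% power, against 0.37 SD for the association with 250 treated, under the assumptions above.
- It removes time, measurement and forum effects, but placebo and expectancy only in part.
- No untreated control remains after week 9, so second-round and 12- and 24-month data cannot support a claim of effect modification.

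The cost is wording and one model term. LSAS is already a study measure, and the efficacy comparison needs a nine-week value from both arms anyway. The protocol names no primary scale, so choosing LSAS for this test is a decision to record. The real price is that the gene question, asked as effect modification, may well end inconclusive.

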**Design**

Two hundred and fifty people diagnosed with social phobia in an experimental study be randomized into two treatment groups: 1) Internet-based CBT (n = 125) or 2) Control group who participate in a moderated discussion forum on the web (n = 125). The control group will be treated with Internet-based CBT after the initial group has completed their treatment, ie. after nine weeks. Genotyping based on saliva samples is done before starting treatment for those who leave the voluntary sample.

**Subjects**

The number of volunteers is estimated at 250 people, 125 in each group. The choice of the number of people based on 125 people in each group is assumed, based on power calculation, be sufficient for this to be a reasonable chance to detect clinically relevant effects if any. The research group's previous genetic analysis of social anxiety disorder have found clinically significant effects detected in even smaller samples (20,22,23), but with 125 people in each group we will have a fair chance to detect effects of gene variants (and gene-gene interactions) on treatment response and symptom profile. The subjects will be recruited through the project's website ([www.studie.nu](https://mail.liu.se/owa/redir.aspx?C=c770dbacb4d543a68289873d76df6c57&URL=http%3a%2f%2fwww.studie.nu)), and via a link on the Anxiety Disorder Society's website. The potential subject will be able to register interest on the study website after taking part of the information (informed consent). It informs also the subject of ethical research principles including that participation is voluntary and that at any time can stop the current treatment. Only persons aged 18 and above will be included.

**Screening, pretreatment assessment and randomization**

The screening process will follow the procedures from our recent study in the SOFIE project (No. 2005:187). When the subject has expressed an interest, a code is sent out which gives access to the portion of the site on which the screening instruments available. The participant answers the first forms: Social Phobia Screening Questionnaire-SPSQ (3) and Montgomery Asberg Depression Rating Scale-MADRS (24). Participants must meet the criteria for social phobia using the international classification system Diagnostic and Statistical Manual of Mental Disorders, 4th edition (DSM-IV) (25). This is mainly determined by SPSQ form that has been shown to have good sensitivity and specificity in comparison with the structured diagnostic interviews. In addition, we include a telephone screening, which follows a structured clinical interview, Structural Clinical Interview for DSM-IV - Axis I Disorders: SCID I (26). Individuals with current major depression and / or suicide-prone persons will be excluded from the study. Furthermore, the subject will be asked to submit a signed consent form to the research group. The constent form involves consent to do genetic analyzes and stores saliva samples in a biobank, the processing of personal data concerning him / her in accordance with the Data Protection Act and that he / she hs received information on the website about how the study.

The subjects meeting the inclusion criteria will then be randomized into two groups so that half may begin directly with the Internet-based self-help treatment program (treatment cycle 1) while the other half gets allocated to the control group which involves participation in a moderated discussion forum on the Internet for nine weeks after which they are treated as usual with the Internet-based program (treatment session 2). The latter group controls in this manner for the time and measurement.

Before the treatment groups may have access to self-help program will fill the subjects in the pretreatment measures consisting of: Social Interaction Anxiety Scale (27), Social Phobia Scale (27), Liebowitz Social Anxiety Scale-LSAS (28), Beck Anxiety Inventory (29), and Quality of Life Inventory (30). All these forms are internationally established and have been shown to have good psychometric properties. Two handwritten forms, which measures the degree of alliance respectively. knowledge acquisition will also be designed and administered during the study period.

**Treatment**

Treatment will be through the Internet in two rounds, and will take advantage of our previously developed structured self-help program that lasts for a total of nine active treatment weeks. The guided self-help program is based on an updated version of the previously used in our approved studies (Ref: 02-555, 03-636, 2004: m-163, 2005:187) ie. on well-proven principles from cognitive behavioral therapy. Following each treatment week participants will be asked a number of questions and send answers via the website to show that they have assimilated the module content. In connection with this they will obtain the password to the next module. Each week, participants also fill in LSAS form and question 9 from MADRS dealing with the zest for life and possible suicidal thoughts. This weekly measurement helps to monitor participants' current state and intervene if needed. All participants will be participate in Internet discussion group where they can speak and send messages to each other. The different treatment groups will have separate discussion groups, which are monitored daily. The degree of anonymity determines the participants themselves, and they may for example choose the username of your choice. The study coordinators will be available to answer questions.Psychology Candidates during the final phase of their education will, according to a well-established model, participate in the project in connection with their MSc theses. As in our previous treatment studies (10-12) they will serve as e-mail therapists under supervision. We have previously evaluated the efficacy of CBT program administered in this way in five randomized controlled trials, of which three have so far been published (10-12) along with an open study (31).

